1	I get short of breath when hurrying on level ground or walking up a slight hill
2	On level ground, I walk slower than people of the same age because of breathlessness
3	On level ground, I have to stop for breath when walking at my own pace
4	I stop for breath after walking about 100 m or after 5 min on level ground
5	I am too breathless to leave the house or I am breathless when dressing

The RISE (Table 2) will be first calculated, as previously described, on a scale from 1 to 3 [3]. However, a modified and improved version of the RISE will also be considered, using the CALIPER-revised CPI instead of the original version of CPI [13], and with a new 1 to 4 scale, which may allow for better stratification for mortality risk (Table 2). If superior to the previous version of RISE, the modified version will be tested for validation.

**Table 2 Tab2:** Risk Stratification Score (RISE) (revised)

RISE components: 1. MRCDS ≥ selected cutoff* 2. 6MWD % pred ≤ selected cutoff* 3. CPI ≥ selected cutoff*	RISE
No parameter met	0
One parameter met	1
Two parameters met	2
Three parameters met	3

MRCDS: MRC dyspnea score; 6MWD: 6-min walk distance; CPI: Composite Physiologic Index (CALIPER-revised version)

^*^selected cut-offs for each variable will be determined by receiver operating characteristics analysis (c-statistics)

Patients will be prospectively followed for a period of 3 years from the time of diagnosis and enrolment. All multi-dimensional scores will be calculated at 4-months intervals corresponding to each visit. A 2nd HRCT will be obtained at the 2-year visit, or sooner if clinically indicated, and as per clinicians’ discretion. The HRCT fibrosis score [12] will be then recalculated on the 2nd scan. Deaths, LTx, AEs and hospitalizations due to respiratory causes will be recorded. All protocol violations (missed visits, delayed visits, data not obtained at individual visits) will be systematically recorded. Every interruption or change in course of therapy will be recorded. When available, hemodynamic data from RHCs will be considered. Since 2D echocardiograms alone are unreliable in predicting the presence of APH in IPF [21], they will not be considered.

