At the end of the study period, both baseline RISE and longitudinal changes of RISE will be tested as predictors of mortality. Other individual variables will also be tested as predictors of mortality, including age at the time of diagnosis, time between onset of symptoms and diagnosis (months), gender, body mass index, smoking history (pack-years), FVC, DLCO, 6MWD (meters and % predicted), desaturation during 6-min walk test, HRCT visual fibrosis score at the time of diagnosis, and other multi-dimensional scores (GAP, CPI, MRSS). In the validation cohort, we will seek to confirm and validate results obtained in the development cohort.

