### Statistical analysis and sample size calculation

The distribution of variables considered will be analysed with Kolmogorov–Smirnov test. Interobserver variability among chest radiologists and lung pathologists will be assessed with Weighted kappa coefficients [29]. Survivors and non-survivors will be compared by using the unpaired t-test, or, for not normally distribute variables, with the Mann–Whitney U-test. To rule out multicollinearity and demonstrate that included variables are truly independent, variance inflation factors of the RISE components will be calculated [30]. Receiver operating characteristics analysis will be used to identify the most accurate cut-off values for each variable to predict endpoints. Multivariate analysis of significant predictors of endpoints will be conducted with the Cox proportional hazard model. Results will be summarized as hazard ratios. Once patients are listed for LTx, death and LTx become competing events. To account for the competing risks of LTx and death in the population of patients undergoing LTx assessment, the Fine-Gray competing risk regression model [31] will be used. This will identify variables significantly predicting independent survival status and results will be summarized as subdistribution hazard ratios. These represent the relative risk of dying prior to LTx. Survival will be further evaluated using Kaplan–Meier curves and the log-rank test. Sample size calculation for an observational, cohort study was conducted using the methodology described by Wang and Ji [32], with the assistance of a statistician. Using available, preliminary data on 109 patients, dropout rate, ratio of low RISE to high RISE, and mortality rates in low RISE and high RISE subgroups were determined. With a power (probability of detecting a real effect) of 90%, and with a conservative approach, a sample size of 125 patients for each cohort was determined to be required.

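### The revised RISE is built from outcome-optimised ROC cut-offs and then tested by ordinary Cox and log-rank methods, so its results are optimistic in the cohort that supplies the cut-offs

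*Protocol article*

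**What the plan says.** All references are to the Protocol article.

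- **Cut-offs.** Statistical analysis and sample size calculation: "Receiver operating characteristics analysis will be used to identify the most accurate cut-off values for each variable to predict endpoints". Methods and design, Table 2 footnote, on the revised RISE: "selected cut-offs for each variable will be determined by receiver operating characteristics analysis (c-statistics". Revised RISE counts how many of three thresholds are met. Table 2 fixes the direction of each: high MRCDS, low 6MWD % predicted, high CPI.
- **Two versions.** The original RISE is computed as it was published. The revised version uses the CALIPER-based CPI: "If superior to the previous version of RISE, the modified version will be tested for validation". The cohort for that comparison is not named.
- **Tests.** Methods and design: "both baseline RISE and longitudinal changes of RISE will be tested as predictors of mortality". Statistical section: "Multivariate analysis of significant predictors of endpoints will be conducted with the Cox proportional hazard model", with Fine-Gray regression for transplant as a competing event, and "Survival will be further evaluated using Kaplan–Meier curves and the log-rank test".
- **Cohorts.** "In the validation cohort, we will seek to confirm and validate results obtained in the development cohort". On size, "a sample size of 125 patients for each cohort was determined to be required", with 90% power, from mortality in low and high RISE subgroups of 109 earlier patients.

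The article does not give the ROC criterion, the cohort that supplies the cut-offs, whether they are held fixed afterwards, or any allowance for the search.

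**The concern.** A log-rank or Cox test assumes that the groups were fixed without looking at the outcome. A ROC-optimal cut-off is chosen because it separates patients with the event from those without it. Comparing survival across it in the same patients counts that separation twice. Three such components, each selected to point towards higher risk, are then added, and the optimism accumulates.

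For the revised RISE this needs no inference about intent: the score does not exist until its cut-offs have been found from outcomes. The plan expects results from the development cohort and sizes each cohort for low versus high RISE.

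Three things are at stake:

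- The development hazard ratio and interval for revised RISE would be misleading.
- The choice between versions could favour the revised score merely because its cut-offs were freshly tuned to the data.
- The validation cohort loses its protective value if cut-offs are found again inside it, which the text does not rule out.

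**Working it through.** **1. The plan's own figure.** The 125 cannot be reproduced, because mortality rates, low:high ratio, dropout and alpha are not given. Assumed inputs can reach it. With 30% versus 60% mortality, 1:1, two-sided 5% and 90% power, the number per group is

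[1.96·√(2·0.45·0.55) + 1.2816·√(0.3·0.7 + 0.6·0.4)]² / 0.3² = (1.379 + 0.860)² / 0.09 ≈ 55.7, so 56.

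That is 112 in total, and 112/0.9 = 124.4, so 125 with 10% dropout. This neither confirms nor refutes the figure. Only n = 125 is used below.

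**2. Inputs to the simulation.**

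- From the article: 125 patients, 3 years of follow-up, three components, directions as in Table 2.
- Assumed: Youden's index as the ROC criterion; two continuous components and one six-level MRC-type score; low/high RISE split at 2; no transplants or dropout; 3-year event rate 30–50%. The Background's mean survival of 3 to 5 years, if exponential, implies 1 − e^(−3/5) = 45% to 1 − e^(−3/3) = 63%. A separate set of runs used those rates.

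**3. Method.** For each component choose c* to maximise J(c) = sensitivity + specificity − 1 for 3-year status. Set RISE to the number of thresholds met. Test in the same patients, rejecting when the log-rank χ² (1 df) exceeds 3.84.

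**4. No true effect: rejections at nominal 5%.**

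| Cut-off search | Event rate | One continuous variable, direction fixed | Direction free | Six-level score | RISE ≥2 vs <2 |
|---|---|---|---|---|---|
| Central 60% | 40% | 15.2% | 31.0% | 5.2% | 23.7% |
| Central 80% | 30% | 20.1% | 37.9% | 7.0% | 32.2% |
| Central 80% | 40% | 19.2% | 37.6% | 6.9% | 32.7% |
| Central 80% | 50% | 17.9% | 34.9% | 7.3% | 31.9% |
| Unrestricted | 50% | 21.1% | 37.4% | 8.8% | 39.3% |

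With cut-offs set beforehand, the same settings give 4.0–5.5% for a single variable and 4.3–5.1% for RISE. The runs at 45–63% mortality, with component correlations of 0.3–0.6, gave 19–32% for RISE 0–1 versus 2–3. A further independent run gave about 24%. Simulation error is small: at 33% with 1,500 runs, √(0.33·0.67/1500) = 1.2 percentage points. The spread comes from the assumptions.

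**5. Does a second cohort of 125 repair it?** No true effect, 40% events, trend log-rank across RISE levels (central 80% search / unrestricted):

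- same patients: 50.7% / 58.9%
- cut-offs frozen, fresh cohort: 5.0% / 6.0%
- cut-offs found again in the validation cohort: 44.3% / 57.5%

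**6. Real effects.** Hazard ratio per point of RISE, compared with the same cut-offs in 4,000 fresh patients (ranges are over the two search rules):

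| True HR per SD of each component | Median development HR | True HR | Coverage of 95% interval | Rejections, development | Rejections, frozen in fresh 125 |
|---|---|---|---|---|---|
| 1.3 | 2.03–2.07 | 1.54 | 65–69% | 99.5–99.9% | 65–66% |
| 1.6 | 2.60 | 2.06–2.07 | 78–79% | 100% | 99% |

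On the log scale the inflation is ln 2.07/ln 1.54 = 0.728/0.432 = 1.68 in the first case and ln 2.60/ln 2.06 = 0.956/0.723 = 1.32 in the second. For a single continuous variable tested at its own cut-off, the median was 2.18 against a true 1.52 and 2.67 against 1.95, with coverage about 84–87%.

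**The case against.** The strongest reply is that the design already contains the standard remedy. A separate prospective cohort is there to confirm the development results, and optimism in development is expected. This stands in part: step 5 shows the error back at about 5–6%, but only if cut-offs are frozen, and the article does not say so. Bootstrap detail may well sit in a fuller document. What the article does state is outcome-optimised cutting followed by ordinary tests.

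A second reply is that the article treats the three domains as established predictors, so a no-effect setting is not its premise. That is fair. For revised RISE the realistic harm is the inflated hazard ratio and poor coverage of step 6 more than false positives.

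A reader might also infer more than the text supports:

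- *That every predictor is tested at its ROC cut-off, so that null variables flow into the Cox model.* The log-rank sentence names no variable, and other groups exist in the plan (UIP pattern, emphysema, antifibrotic drug). The same section compares survivors with non-survivors by t-test or Mann–Whitney on the measured scale, and Cox can take continuous predictors.
- *That RISE itself is ROC-cut, or that both versions are affected.* Only the components of the revised version are said to be cut this way. The original is not said to receive new cut-offs.
- *That 19–37% is this plan's error rate.* That range fits one continuous variable with no effect under assumed search settings. Its upper end needs a free direction, whereas Table 2 fixes direction for the RISE components.
- *That the 90% power is meaningless.* The 125 also applies to the validation cohort, where a frozen-cut-off test is a proper test.

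**Conclusion.** The point holds for the revised RISE in the cohort where its cut-offs are found. Ordinary p-values there are too small, hazard ratios too large and intervals too narrow. With 125 patients, no true effect and Youden cut-offs, a nominal 5% log-rank test of RISE ≥2 versus <2 errs about 20–40% of the time. With real effects of 1.3–1.6 per SD, the per-point interval covers about 65–79% of the time.

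It holds conditionally for any other continuous variable tested at its own ROC cut-off in the same patients: about 19% error with direction fixed and about 35% with direction free, but only 5–10% for an ordinal MRC-type score. It does not touch the original RISE unless that is re-cut.

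The sizes rest on the ROC criterion, search range, event rate and low/high split, none of which the article gives. Fine-Gray analysis was not simulated. The direction of the bias does not depend on these choices. The validation cohort limits the damage, provided the cut-offs are frozen, so this is a defect to correct and does not invalidate the design.

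**What to change.** - State that all cut-offs are derived in the development cohort only and applied unchanged in the validation cohort.
- Test continuous predictors in Cox on their measured scale.
- Report development-cohort estimates for revised RISE with a bootstrap that repeats the whole cut-off search in each resample, or label them exploratory. Use the corrected figures when judging whether the revised version is superior.
- Attach the confirmatory RISE test, and the 90% power, to the validation cohort.

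This needs changes of wording and a modest amount of programming, with no new data or patients. The downside is that development results will look less favourable and the bootstrap is a little more work.

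### Statistical significance decides which of 16 overlapping candidates enter the Cox model, at fewer than about 5 deaths per candidate, and no adjustment set is fixed for the two cohorts

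*Protocol article*

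**What the plan says.** The section Statistical analysis and sample size calculation gives the entry rule: "Multivariate analysis of significant predictors of endpoints will be conducted with the Cox proportional hazard model". It names no threshold and no fixed covariates, and does not say that RISE is always in the model.

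Methods and design supplies the candidates. It says that "both baseline RISE and longitudinal changes of RISE will be tested as predictors of mortality", and then: "Other individual variables will also be tested as predictors of mortality, including age at the time of diagnosis". The list continues with symptom-to-diagnosis interval, gender, body mass index, pack-years, FVC, DLCO, 6MWD in metres and as % predicted, desaturation, HRCT fibrosis score and three other composite scores (GAP, CPI and MRSS).

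On the second cohort the same section says: "In the validation cohort, we will seek to confirm and validate results obtained in the development cohort". On size, the statistics section says that "a sample size of 125 patients for each cohort was determined to be required". Its collinearity check (variance inflation factors) covers the RISE components only.

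**The concern.** This is a rule that the article states, not a detail left for later: an analysis plan that followed the sentence would carry it out. Three things make it fragile here.

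- **Overlap.** By the article's own descriptions (Table 2 and Discussion), FVC and DLCO feed both CPI and GAP, FVC also feeds MRSS, CPI and 6MWD feed RISE, and 6MWD is listed twice in different units. Which of several near-duplicates passes a significance screen is partly chance.
- **Few deaths per candidate.** A moderate predictor may pass or fail through sampling variation alone.
- **Confidence intervals.** Those from the final model treat the chosen set as if it had been fixed in advance.

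At stake is the adjusted hazard ratio of RISE. The study hypothesises that RISE is the best predictor and relies on two cohorts to establish it. Under this rule, what RISE is adjusted for depends on which variables happened to pass.

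**Working it through.** **The plan's own figure.** The 125 per cohort can be neither reproduced nor refuted. The article gives the power ("With a power (probability of detecting a real effect) of 90%, and with a conservative approach") but not alpha, the low-to-high RISE ratio, the subgroup mortality rates or the dropout. Assuming two-sided 0.05, 90% power, a high-RISE share of 20–50% and five plausible pairs of low/high mortality, a two-proportion formula gives a total of 60–170 (67–189 after 10% dropout), and the Schoenfeld formula gives 55–207. The figure of 125 lies inside each range. It is taken as given. As described, it is sized on low versus high RISE, not on a multivariable model.

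**Candidates.** 2 RISE terms (baseline, change) + 11 individual variables + 3 other scores = 16.

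**Deaths per cohort.** The article states no number. Its Background gives an untreated mean survival of 3 to 5 years. Assuming exponential survival, deaths = 125 × (1 − exp(−3/m)):

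| Mean survival m (years) | 3-year mortality | Deaths | Deaths ÷ 16 |
|---|---|---|---|
| 3 | 0.632 | 79 | 4.9 |
| 4 | 0.528 | 66 | 4.1 |
| 5 | 0.451 | 56 | 3.5 |

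These take no account of dropout, censoring at transplant or anti-fibrotic treatment. An assumed 3-year mortality of 20–60% gives 25–75 deaths, or 1.6–4.7 per candidate. If transplants were counted as events, the counts would rise by a number that the article does not give.

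**Effect of the rule, by simulation.** Each cohort had n = 125 and 16 normally distributed candidates, of which 11 were null. The pairwise correlation was 0 or 0.3, and mortality was 30%, 45% or 63% (about 38, 56 and 79 deaths). Candidates with univariable p < 0.05 entered a multivariable Cox model. There were 150 pairs of cohorts per scenario. The five true effects were either all HR 1.30 per SD, or one of 1.60 with four of 1.20.

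*Stability.* When selection was run separately in each cohort, the two selected the identical set in 0–7% of pairs. The terms also significant in the multivariable model were identical in 1–20% of pairs.

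*Mean hazard ratio of one true predictor:*

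| True HR | Correlation | When selected | Selected and also significant in the multivariable model |
|---|---|---|---|
| 1.30 | 0 | 1.40–1.56 | 1.42–1.62 |
| 1.30 | 0.3 | 1.31–1.33 | 1.52–1.79 |
| 1.60 | 0 | 1.60–1.69 | 1.60–1.71 |
| 1.60 | 0.3 | 1.60–1.62 | 1.67–1.84 |

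The largest excess for the strong predictor is 1.84/1.60 = 1.15, about 15%.

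*No selection.* Fitting all 16 candidates also overstated the effects: 1.34–1.38 for a true 1.30, and 1.68–1.77 for a true 1.60. Entering every candidate is therefore no remedy.

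**The case against.** The other side has several good points.

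**Rerunning selection is not stated.** A reader might infer that the two cohorts will adjust for different variables. The article says only that the second cohort is to confirm the first. It says neither that selection is repeated nor that the development model is applied unchanged. This stands, so the 0–7% agreement applies only if selection is rerun. The entry rule remains a weakness either way, because a set carried over would itself have been chosen partly by chance.

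**Inflation is not general.** A reader might infer that adjusted hazard ratios, including that of RISE, are inflated across the board. A calculation for one isolated predictor under independence (true HR 1.30, standard error 1/√50) does give a mean of 1.47 when significant. It is not an adjusted hazard ratio, and the real candidates overlap. With correlation 0.3 the mean when selected falls to 1.31–1.33. It is large again only if reporting is confined to terms significant in the multivariable model, which the article does not say. No material bias in the RISE hazard ratio has been shown.

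**The number of deaths is not small in itself.** The article's survival statement allows 56–79. The problem is deaths per candidate.

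**RISE is not built by this step.** Its three components are fixed in Table 2 and its cut-offs come from ROC analysis. Several of the 16 are named as comparators for RISE and are not clearly adjustment covariates. That is correct, but the article never separates the two roles, and the entry rule applies to all of them.

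**A condensed article leaves detail to an analysis plan.** That would excuse a missing threshold or covariate list. It does not excuse a stated rule that significance decides entry.

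**Conclusion.** The concern holds in a limited form. The article lets significance choose the multivariable model from 16 overlapping candidates, with about 3.5 to 4.9 deaths per candidate on its own untreated survival figures and fewer at lower mortality. It fixes neither the adjustment set nor how that set passes to the validation cohort. The selected set is unstable, its confidence intervals ignore the selection, and estimates for weak or moderate predictors retained for significance tend to be biased away from 1. In the scenarios examined, that bias ran from almost nothing (1.31 for a true 1.30) to substantial (1.79 for a true 1.30). For a strong predictor it ran from none to about 15%.

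The documents do not support saying that the cohorts will have different models, or that the RISE hazard ratio is inflated. The death counts assume exponential survival, and the simulation figures depend on assumed effects, correlations and a 5% entry threshold. The candidate count and the entry rule come directly from the text.

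**What to change.** **Adjusted analysis of RISE.** Replace entry by significance with a short adjustment set fixed before outcomes are examined. It should consist of baseline variables already collected that are not RISE components, for example age, gender and pack-years. Enter them whatever their p-values, always include RISE, and use the same model specification in both cohorts. With RISE as a single term, that makes 4 terms: 56/4 = 14 to 79/4 ≈ 20 deaths per term. With RISE as a four-level factor it makes 6 terms: 56/6 ≈ 9 to 79/6 ≈ 13.

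**Comparisons.** For GAP, CPI, MRSS, pulmonary function, 6MWD and HRCT score, prespecify head-to-head models containing RISE plus one comparator. This keeps the joint test that the hypothesis needs. Leave out of the adjustment set any variable that is an input of that comparator: age and gender for GAP, age for MRSS.

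**Reporting.** Give every candidate with its confidence interval, whether or not it is significant.

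**Cost.** A few sentences and no new data. The downside is a few degrees of freedom spent on covariates that may prove weak.

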### Ethics approval and consent to participate

The study was approved by the Research Ethics Board of Western University (protocol n. 107131) and of University of Rome “Tor Vergata” (protocol n.171.15). The study is a registered clinical trial (identifier: NCT02632123) at the U.S. National Library of Medicine clinicaltrials.gov registry.

Informed, written consent is required from all participants. A letter of information and consent form is provided to each patient prior to entry to the study. The investigator will answer any questions the patient has regarding the involvement in the study or the study protocols. Consent forms with identifiable information will be stored in a locked office on site. Participants will be assigned an identifier number at the time of study entry. All study records will identify the participant by the identifier number only. All personal information will remain confidential. Patients will be informed that they are free to withdraw from the study at any time.

